## Abstract

**Background:**

The care needs of patients with a limited prognosis (<12 months median) are complex and dynamic. Patients and caregivers must cope with many challenges, including physical symptoms and disabilities, uncertainty. and compromised self-efficacy. Healthcare is often characterized by disruptions in the transition between healthcare providers. The Milestones Communication Approach (MCA) is a structured, proactive, interprofessional concept that involves physicians and nurses and is aimed at providing coherent care across the disease trajectory. This study aims to evaluate these aspects of MCA: (1) the training of healthcare professionals, (2) implementation context and outcomes, (3) patient outcomes, and (4) effects on interprofessional collaboration.

**Methods/design:**

A multiphase mixed-methods design will be used for the study. A total of 100 patients and 120 healthcare professionals in a specialized oncology hospital will be involved. The training outcomes will be documented using a questionnaire. Implementation context and outcomes will be explored through semi-structured interviews and written questionnaires with healthcare professionals and with the training participants and through a content analysis of patient files. Patient outcomes will be assessed in a pragmatic non-blinded randomized controlled trial and in qualitative interviews with patients and caregivers. Trial outcomes are supportive care needs (SCNS-SF34-G), quality of life (SeiQol and Fact-L), depression and anxiety symptoms (PHQ-4), and distress (Distress Thermometer). Qualitative semi-structured interviews on patients’ views will focus on shared decision-making, communication needs, feeling empathy, and further utilization of healthcare services. Interprofessional collaboration will be explored using the UWE-IP-D before the implementation of MCA (t0) and after 3 (t1), 9 (t2), and 12 (t3) months.

**Discussion:**

Using guideline-concordant early palliative care, MCA aims to foster patient-centered communication with shared decision-making and facilitation of advance care planning including end-of-life decisions, thus increasing patient quality of life and decreasing aggressive medical care at the end of life. It is assumed that the communication skills training and interprofessional coaching will improve the communication behavior of healthcare providers and influence team communications and team processes.

**Trial registration:**

German Clinical Trials Register, DRKS00013649 and DRKS00013469. Registered on 22 December 2017.

**Electronic supplementary material:**

The online version of this article (10.1186/s13063-018-2814-1) contains supplementary material, which is available to authorized users.

## Background

The care of patients with a limited prognosis is complex and demanding. Moreover, the process of care is often interrupted by quick transitions between healthcare settings and providers, especially for cancer patients [1], leading to a lack of continuity in care. Throughout the disease trajectory, patients and caregivers must deal with receiving bad news at short intervals. The terminal character of a limited prognosis means that patients need to engage in advance care planning and end-of-life decision-making. Therefore, patients and their caregivers must deal with several dimensions of burden (physical, psychological, social, financial, and spiritual) [2].

The quality of care for patients with advanced cancer hinges, among other factors, on the communication skills of the healthcare professionals involved. Delivering bad news, discussing prognoses and possible disease trajectories (best case and worst case), and preparing others for the end of life are challenging communication topics and demand highly skilled professionals [3]. Yet, patients, caregivers, and the healthcare professionals themselves often perceive these skills to be insufficient [4, 5].

The German National Cancer Plan [6] and other medical societies recommend that healthcare providers should improve their communication skills [6–8]. Indeed, different communication training programs have been developed and evaluated successfully for the medical curriculum [9, 10]. Yet, most of these programs focus on basic communication skills in specific situations [11–14] without considering the whole disease trajectory. Furthermore, communication modules concerning palliative care have been developed but refer mainly to the transition to the best supportive care for the terminally ill [15]. The positive results of trials regarding the early integration of palliative care [16, 17] additionally challenge patient–physician communications as they leave the oncologist with the task of addressing palliative care early in the course of disease.

These trials and others that evaluate the training of communication skills in oncology have shown multiple benefits: improvement of quality of life and advance care planning for patients, improvement in job satisfaction, and decrease of burden on professionals [12, 13, 18–21]. Additionally, different studies on palliative care show that multi-professional approaches are more effective [16, 22–24].

For advanced lung cancer, forward-thinking communication has been described for the German setting [25]. This introduces standardized steps of communication at turning points of treatment, such as first disclosure of diagnosis, disease progression, and transition to best supportive care. Based on findings from interviews with patients and caregivers and focus groups with healthcare professionals, a structured longitudinal concept has been developed: the Heidelberg Milestones Communication Approach (MCA) [5, 26, 27].

MCA is a pro-active, interprofessional concept that involves physicians and nurses and is aimed at providing coherent care that integrates palliative care early and across the disease trajectory. It provides intervention-based communication to develop patient-centered care further through increasingly integrating patient preferences. Metastatic lung cancer has been used as a model disease in developing MCA. Not only is there a limited prognosis with a median survival of less than 12 months but it is also associated with a substantial existential uncertainty and a high symptom burden with detrimental impact on patients and caregivers [27, 28]. However, institutional strategies for implementing longitudinally structured communication concepts such as MCA and knowledge about the effects of implementation are still lacking.

Many interventions in clinical and health services research fail to translate into practice and policy [29]. Implementation processes are complex, take a long time, and are cost intensive [30, 31]. Therefore, the effects and implementation of an intervention need to be evaluated concurrently. Furthermore, implementations are influenced by individual health, professional factors, patient factors, professional interactions, incentives and resources, capacity for organizational change, as well as by social, political, and legal factors [32].

### Aims and objective

This study aims to evaluate these aspects of MCA:training of healthcare professionalsimplementation context and outcomespatient outcomeseffects on interprofessional collaboration.

## Methods/design

### Multiphase mixed-methods design

Since several perspectives (patient, family caregiver, and healthcare professional) and different interventions (communication concept, training, and implementation) at different stages (development, implementation, and evaluation) are relevant, a mixed-methods design has been chosen [33–35]. Our aims contain complex multidimensional processes (social, cognitive, and cultural) and multiple stakeholders (patients, caregivers, and healthcare professionals). To evaluate outcomes, a randomized controlled trial (RCT) and interviews with patients and caregivers are planned. To evaluate processes and context, a combination of quantitative and qualitative methods will be applied [35]. The multiphase mixed-methods design allows a comprehensive understanding of the effects of MCA [34].

### Phase 1: development of the Heidelberg MCA

Our previous studies in phase 1 included a qualitative exploration of patients’ and caregivers’ experiences over the disease trajectory and the assessment of healthcare professionals’ views of a hypothetical structured and forward-thinking communication approach [5, 26, 27]. Based on these results, Heidelberg MCA was developed as a complex intervention: (a) to address the communication needs of patients and caregivers, (b) to improve continuity of care, (c) to improve individual quality of life of patients and their caregivers, (d) to foster shared decision-making including end-of-life decisions, and (e) to enhance communication competencies and team processes of the interprofessional oncology team.

In a second step, we led in-depth interviews with nurses and focus group interviews with physicians at our institution to explore the enablers and barriers of implementation as well as interprofessional collaboration concerning all four components of MCA. Based on the results of these interviews, MCA was adapted and now contains the following components (see Table 1):

**Table 1 Tab1:** MCA complex intervention components

Intervention component	Subcomponent	Content
Communication training	Two training sessions with simulated patients and video assessment Two training sessions in a clinical setting including individualized feedback Coaching	MCA conversation components Communication skills Attitude Empathy Prognostic awareness
Milestone conversations	Diagnosis	Breaking bad news Treatment options Outlining follow-up and contact with nurse
	Stable phase	Question-prompt-list Prognostic awareness Advance care planning Palliative care needs
	Progression	Question-prompt-list Breaking bad news Prognostic awareness Treatment options Advance care planning Palliative care needs
	Transition to best supportive care	Question-prompt-list Breaking bad news Prognostic awareness Advance care planning Symptom treatment Palliative care needs
Follow-up sessions	Patient is contacted every month by telephone or during a routine clinic visit by a nurse	Palliative care assessment Prognostic awareness Answering patient questions Referrals if necessary
Material	Communication manual for milestone conversations	Content of milestone conversations Training material
	Memory cards	Quick overview of milestone conversations
	Managing symptoms guidebook	Brochure for patients on symptom management
	Question-prompt-list	Questions patients could ask

*MCA* Milestones Communication Approach

1. Interprofessional (physician and nurse) communication training

2. Planned, structured nurse-physician-patient and caregiver conversations at four points within the disease trajectory, the so-called milestone conversations

3. Monthly follow-up sessions for outpatient and ambulatory patients and their caregivers (nurse)

4. Supportive materials (question-prompt-list, managing symptoms guidebook for patients and caregivers, and communication manual and memory cards for nurses and physicians)

For a more detailed description of the intervention, see Additional file 1.

No harm is anticipated from the intervention. If any harm is identified, a referral to psycho-oncology services is possible.

The complete project consists of three phases: (1) further development, (2) implementation, and (3) evaluation. Phase 1 (further development) had a separate ethical approval (ethics committee University of Heidelberg S-139/2017) and is already completed. This study protocol is for phase 2 (implementation) and phase 3 (evaluation). Implementation and evaluation are based on the results of phase 1. During the implementation phase, communication training will be conducted and evaluated. Implementation of MCA will be adapted according to participant experiences. The evaluation phase includes a monocentric non-blinded RCT measuring the effects of MCA in patients with a limited prognosis. In a cohort study, the longitudinal effects on interprofessional collaboration of clinical staff will be observed. Experiences with the concept will be evaluated in qualitative semi-structured interviews with patients and their caregivers (see Table 2).

**Table 2 Tab2:** Study aim, method, type of data, and outcome

	Study aims	Methods	Participants	Outcomes	Type of data
Phase 2 implementation	Evaluation of communication training	Questionnaire	Physicians and nurses	Training success	Quantitative
	Evaluation of implementation context and outcomes	Interview and focus group interviews	Physicians and nurses	Fidelity and adherence enablers and factors associated with implementation	Qualitative
		Quantitative content analysis of patient electronic files		Adherence	Quantitative
Phase 3 outcome evaluation	Impact of MCA on patient outcomes	Pragmatic RCT using questionnaire	Patients and caregivers	Supportive care needs Patient quality of life Patient distress	Quantitative
		Semi-structured interviews	Patients and caregivers	Patient reported outcomes	Qualitative
	Evaluation of effects on interprofessional collaboration	Questionnaire	Healthcare professionals	Attitudes towards interprofessional collaboration	Quantitative

*MCA* Milestones Communication Approach, *RCT* randomized controlled trial

To implement MCA, it is important to understand how MCA works within a real-life clinical setting. This implementation implies working with healthcare professionals who will be affected by MCA and investigating the context of the intervention. A hospital context is not a fixed organizational structure but an unstable, unfolding process [36]. Thus, implementation of MCA will be conducted using a plan-do-check-act (PDCA) cycle [37].Plan: Plan communication training and a theory-based implementationDo: Conduct communication training and make first attempts at using MCACheck: Investigate experiences with trained nurses and physiciansAct: Reintegrate evaluation results into everyday MCA practice

If necessary, the PDCA cycle will be used several times. This approach ensures that the adaptability, usability, and feasibility of MCA are incorporated [32].

#### Setting

The project will be conducted at the Department of Thoracic Oncology, University Hospital Heidelberg, which is one of the largest lung cancer centers in Germany. Every year, about 600 patients are newly diagnosed with metastatic lung cancer. The physicians involved in the project are oncologists and residents in advanced oncology, working mainly at the outpatient clinic. Their daily consultations include the first disclosure of diagnosis and prognosis, disclosure of progression, and transition to best supportive care (breaking bad news). The nurses have working experience in oncology and palliative care in both inpatient and outpatient settings.

### Phase 2: implementation

#### Evaluation of communication training outcomes

##### Questionnaire for training evaluation

To explore training, acceptance level 1 (reaction) and level 2 (learning) of the Kirkpatrick model will be evaluated [38]. The sample includes five nurses and five physicians, who will receive the training. To integrate MCA communication content, participants will complete a self-assessment questionnaire with 26 items on acquisition of intended knowledge, skills, attitude, confidence, and commitment based on participation in the training and relevance to participants’ work. Items are rated on a five-point Likert scale ranging from agree completely (1), agree (2), neither agree nor disagree, disagree (4) to disagree completely (5). In addition, there are four open-ended questions on what participants liked best or least about the training, their overall impression, and what would help to enhance their communication skills. Training participants (*n* = 10) will be invited to complete the questionnaire after all four training sessions. The questionnaires will be analyzed using descriptive statistics, including mean, median, standard deviation, and range. Thematic analysis will be used to evaluate open-ended questions [39]. The results of each training session will be used to plan and improve the next training session.

#### Evaluation of implementation context and outcomes

##### Interviews to evaluate implementation

Interviews and focus group interviews with training participants will be conducted between the training sessions to explore participants’ experiences with and transfer of MCA into everyday practice. A topic guide derived from the literature and our previous studies will be developed to determine experiences and context factors that influence training, communication, implementation, and collaboration [40]. The main issues raised in the interviews will be recorded on a protocol sheet, summarized, and the results fed back by the researchers to the communication training and implementation team [41]. The results will be used to improve the next training sessions, to enhance implementation in everyday practice, and to adapt both MCA materials (communication manual, memory cards, question-prompt-list, and brochure) and the implementation plan following the PDCA cycle.

##### Quantitative content analysis of patient files

From kickoff, nurses will document excerpts from the milestone conversations and follow-up calls in patient electronic files. Excerpts written 6 months after kickoff (*n* = 50) from the milestone conversations and (*n* = 50) from the follow-up calls will be analyzed for adherence to the MCA concept, shared decision-making, prognostic awareness, and documented topics [41]. The file content will be analyzed using a fidelity checklist of essential topics based on the MCA manual. Data will be entered into SPSS and descriptive statistics will be produced. Binary and continuous variables will be evaluated by mean, median, minimum, and maximum, and categorical variables using absolute and relative frequencies [41]. The results will help to determine to what extent the developers’ intentions regarding training contents and adherence to the communication manual are seen in practice.

### Phase 3: outcome evaluation

#### Impact of MCA on patient outcomes

The effects of MCA on patients and caregivers will be determined in a RCT. Their experiences with the concept will be assessed in semi-structured interviews. The effects on interprofessional collaboration will be evaluated in a longitudinal observational study with healthcare professionals.

#### Effects on patients and caregivers (pragmatic RCT)

In the RCT, the effects of MCA on patients and caregivers will be assessed and evaluated with a focus on shared decision-making and on early and proactive advance care planning. Patients and their caregivers will report on daily life activities and the identification and treatment of palliative care needs. The impact of the concept regarding empathy, quality of life, and distress in patients with metastatic lung cancer will also be examined. Furthermore, needs-based use of services and the impact of further contacts in the German healthcare system will be assessed.

##### Primary outcome

The primary outcome is the effect of MCA on meeting patients’ information needs measured using the health system and information needs dimension of the Supportive Care Needs Survey: Short Form for Patients (German version) (SCNS-SF34-G).

##### Secondary outcomes

The secondary outcomes are the effects of MCA on perceived empathy, quality of life, and distress in patients with metastatic lung cancer and a limited prognosis, needs-based use of health services, and further contacts with healthcare professionals in the German healthcare system.

##### Sample and sample size

The study will consist of 100 patients and 100 caregivers named by the patients. It will include patients with newly diagnosed metastatic lung cancer (stage IV) who are at least 18 years old, able to give consent, have a good knowledge of the German language, and are willing to participate. Participating caregivers also must be at least 18 years old, have a good understanding of the German language, be willing to participate, and give consent.

##### Data collection

Recruitment of patients and caregivers will take place at the Department of Thoracic Oncology, University Hospital Heidelberg. Patients and caregivers will be approached by a study nurse who works at the department. If patients and caregivers are interested in the project, they will receive oral and written information about the study. After giving consent, baseline (t0) questionnaire data will be collected before patients are randomly assigned to a group. The first milestone conversation (tandem or standard communication with a physician) will then take place. For the follow-up, questionnaires will be distributed after 3 (t1), 6 (t2), and 12 (t3) months (Fig. 1). Study plan according to SPIRIT-checklist see Fig. 2 and Additional file 2. Patient documents will be checked by a study nurse for adverse events. No adverse events are anticipated.

**Fig. 1 Fig1:**
[figure not shown]
Flow diagram for patient recruitment

**Fig. 2 Fig2:**
[figure not shown]
Study plan

##### Randomization procedure

The randomization into the groups (intervention and control) will occur in the ratio 1:1. Block randomization will be performed to ensure equal-sized groups. The randomization will be performed using sealed opaque randomization envelopes, which will be provided by the Institute of Medical Biometry and Informatics Heidelberg.

##### Instruments

All instruments are validated in German. Table 3 provides an overview of the assessment instruments. The supportive care needs of patients will be assessed using SCNS-SF34-G. The questionnaire comprises 34 items and covers five domains: (1) health system and information, (2) psychological, (3) physical and daily living, (4) patient care and support, and (5) sexual needs. Patients indicate on a five-point scale if and to what degree they are in need of support (1 not applicable; 2 no need, satisfied; 3 low need; 4 moderate need; or 5 high need) [42]. Subscale scores are obtained by calculating the mean of scale items. The higher the subscale score, the higher the need for support in the respective domain [43].

**Table 3 Tab3:** Outcomes and instruments

Outcome	Instrument
Supportive care needs	SCNS-SF34-G (for patients) [42] SCNS-P&C-G (for caregivers) [44]
Patient quality of life	SEIQoL-Q [46] FACT-G, FACT-L [47, 48]
Depression and anxiety	PHQ-4 [47]
Patient distress	Distress thermometer [56]

*FACT-G* Functional Assessment of Chronic Illness Therapy: general, *FACT-L* Functional, Assessment of Chronic Illness Therapy: lung cancer, *PHQ-4* Patient Health Questionnaire: short form (four questions), *SCNS-P&C-G* Supportive Care Needs Survey for Partners and Caregivers (German version), *SCNS-SF34- G* Supportive Care Needs Survey: Short Form for Patients (German version), *SEIQoL-Q* Schedule for the Evaluation of Individual Quality of Life

The supportive care needs of caregivers will be measured using the German version of the Supportive Care Needs Survey for Partners and Caregivers (SCNS-P&C-G). The multidimensional questionnaire consists of 45 items in four domains: (1) healthcare service needs, (2) psychological and emotional needs, (3) work and social needs and (4) information needs, which are assessed on a five-point scale (1 I have no problems, 2 I am already supported, 3 low need, 4 moderate need, and 5 high need). Answers 1 and 2 are grouped together so that 1 stands for “there is no need for support.” For supportive care needs domains, the mean of the respective items will be calculated, ranging from 1 to 5 [44], and standardized on a 0–100 scale [45].

A patient’s quality of life will be assessed using the Schedule for the Evaluation of Individual Quality of Life (SEIQoL-Q) [46], the Functional Assessment of Chronic Illness Therapy (basic module, FACT-G, and additional questions on lung diseases, FACT-L) [47, 48]. The Patient Health Questionnaire (PHQ-4) [49] will be used to assess depression and anxiety in patients. The SEIQoL-Q measures each patient’s quality of life by choosing, rating, and weighting five domains that patients consider important, such as family, health, or social life/other relations [50]. The five-point scale ranges from not at all (0) to extremely (100) important. Following this, patients must evaluate their overall satisfaction with the areas of life on the same scale [51].

FACT-G consists of 27 items in four domains: (1) physical well-being, (2) social well-being, (3) emotional well-being, and (4) functional well-being. All domains, except emotional well-being, consist of seven items, each with a score in the range 0–28. Emotional well-being contains six items and has a score range of 0–24. For all questions in FACT-G, a five-point rating scale from 0 to 4 (0 not at all, 1 a little bit, 2 somewhat, 3 quite a bit, and 4 very much) is used. The total score for FACT-G is calculated as the sum of the four subscale scores, provided that the overall item response is at least 80% (i.e., at least 22 of the 27 items were answered) and takes values between 0 and 108. Negatively expressed items are reverse scored prior to summing so that higher subscale and total scores indicate a better quality of life [47, 48, 52]. FACT-L contains the four domains of FACT-G and one lung cancer symptom-specific subscale. The seven items of the lung cancer subscale assess patient-reported symptoms, like shortness of breath and loss of weight. FACT-L is also rated on a five-point Likert-scale ranging from 0 (not at all) to 4 (very much) with a score ranging from 0 to 28 [53].

PHQ-4 is an ultra-brief self-report questionnaire that contains a two-item depression scale (PHQ-2) and a two-item anxiety scale (GAD-2) [49]. Patients assess how many times over the past 2 weeks they have felt a loss of interest and happiness, depression, melancholy or hopelessness, nervousness, anxiety or concern, and restlessness. The ordinal-scaled answer options are not at all (0), several days (1), more than half the day (2), and nearly every day (3) [54]. The total score for PHQ-4 ranges from 0 to 12, with categories of psychological distress being none (0–2), mild (3–5), moderate (6–8), and severe (9–12) [55].

Patient distress will be measured using the NCCN Distress Thermometer. This assessment technique was developed by the National Comprehensive Cancer Network (NCCN) and is a brief self-reported screening instrument for recording psycho-social stress in oncological patients. It consists of a scale from 0 to 10 and a problem list. A score of 5 or higher indicates that a patient is conspicuously stressed and needs assistance [56]. If the burden is low (0–4), no additional professional support is required [56].

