##### Data analysis

All baseline patient characteristics will be analyzed descriptively. Continuous variables will be described as means with standard deviation or as medians with interquartile range, minimum, and maximum. Categorical variables will be described in absolute and relative frequencies.

The sum of the health system and information dimension score of SCNS-SF34-G is defined as the primary outcome of the RCT. The primary outcome at t1 will be analyzed using a linear model in which the outcome value is included as dependent variable and the respective baseline value and the treatment group as independent variables. Missing values in the primary outcome will be replaced by multiple imputation, which consider treatment the group and primary outcomes at t0 as independent variables using the fully conditional specification method [57]. A complete case analysis will be performed as an additional sensitivity analysis. The respective parameter estimates will be reported together with *p* values and 95% confidence intervals. The analysis of the primary outcomes at t2 and t3 will be done analogously to the primary linear model. The analyses of the secondary outcomes will be performed using linear (for continuous outcomes) or generalized linear models (for binary outcomes). The models include the outcome value at follow-up time t1, t2, or t3 as the dependent variable. The respective parameter estimates will be reported alongside descriptive *p* values and 95% confidence intervals. *p* values smaller than 0.05 will be considered statistically significant. Analysis will be done using the statistical software SAS v9.4 (SAS Institute, Cary, NC).

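### The patient need score ranks a satisfied need above a not-applicable one, so the primary outcome could understate MCA's effect if MCA makes more topics applicable than standard care does

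*Protocol article*

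**What the plan says.** All references are to the Protocol article.

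- **Patient coding and scoring (Instruments).** Items of the SCNS-SF34-G are answered "1 not applicable; 2 no need, satisfied; 3 low need; 4 moderate need; or 5 high need". The rule is "Subscale scores are obtained by calculating the mean of scale items", and the direction is "The higher the subscale score, the higher the need for support in the respective domain". No merging of codes 1 and 2 is stated for patients.
- **Caregiver scoring (same section).** For the SCNS-P&C-G, "Answers 1 and 2 are grouped together so that 1 stands for" an absence of need for support. The domain mean is then put on a 0–100 scale.
- **Aim (Primary outcome).** "The primary outcome is the effect of MCA on meeting patients’ information needs", measured on the health system and information dimension.
- **Analysed variable (Data analysis).** "The sum of the health system and information dimension score of SCNS-SF34-G is defined as the primary outcome of the RCT". The t1 value is modelled on treatment group and the baseline value.
- **Intervention content (Table 1).** Milestone conversations and nurse follow-up cover prognostic awareness, advance care planning and palliative care needs. They are supported by a question-prompt-list, described as "Questions patients could ask".

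**The concern.** On the stated aim, a patient whose information need has arisen and been met is a success. That patient answers 2. A patient for whom the topic never arose answers 1. The score treats the first patient as having more need than the second, so the step from 1 to 2 adds something to the primary outcome that is not unmet need.

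This would do no harm to the comparison if the two codes were used equally in both arms. MCA, however, is built to bring topics up. If it turns not-applicable answers into satisfied ones more often than standard communication does, the MCA mean rises for a reason that has nothing to do with unmet need. The baseline covariate cannot remove this: t0 is collected before randomisation and before the first milestone conversation, and the shift would come afterwards.

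At stake is the reading of a null or attenuated primary result. Without a planned analysis that neutralises the 1/2 step, one could not tell whether MCA failed to reduce unmet need or whether the scoring hid part of the reduction. A re-scoring chosen after seeing the data would carry little weight.

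**Working it through.** **1. The plan's own sample size.** Inputs from Power calculation: difference 5 on a 0–100 scale, SD 7.4, two-sided α = 0.05, power 0.85, dropout 18.5%. Allocation is 1:1 (Randomization procedure).

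- Normal approximation: n per arm = 2(1.960 + 1.036)² × 7.4² / 5² ≈ 39.3, so 40 per arm and 80 in total. 80 / (1 − 0.185) = 98.2, so 99.
- Exact noncentral t: 41 per arm (power 0.856; 40 per arm gives 0.847), 82 in total. 82 / 0.815 = 100.6, so 101.

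The stated 100 reproduces. The sample size is not in question. It supplies the 5-point yardstick used below.

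**2. Size of one coding step.** Assume linear rescaling, (code − 1) / 4 × 100. The article states 0–100 standardisation only for the caregiver score, but Power calculation puts the primary outcome on 0–100. Codes 1 to 5 become 0, 25, 50, 75 and 100.

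- 1 to 2: +25 on that item (scored as worse).
- 3 to 2: −25. 4 to 2: −50. 5 to 2: −75 (all scored as better).

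One item moving from 1 to 2 therefore cancels one item moving from 3 to 2. Whether the dimension is summed (Data analysis) or averaged (Instruments) makes no difference to this: with the same items answered, one is a multiple of the other.

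**3. Effect on the arm difference.** Let f be the net between-arm share of domain items that move from 1 to 2 in the MCA arm beyond those that do so in the control arm. The MCA mean then rises by 25f relative to control. Suppose the benefit from all other moves equals the 5-point target. Power uses 41 analysed per arm and an unchanged SD of 7.4.

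| f (assumed) | 25f | Net benefit left, 5 − 25f | Power |
|---|---|---|---|
| 0% | 0 | 5 | 0.86 |
| 5% | 1.25 | 3.75 | 0.62 |
| 10% | 2.5 | 2.5 | 0.33 |
| 15% | 3.75 | 1.25 | 0.12 |
| 20% | 5 | 0 | 0.05 |

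The power column does not credit the baseline covariate, which the protocol expects to raise power.

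**4. With codes 1 and 2 merged.** A move from 1 to 2 contributes 0 at every f.

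**The case against.** The strongest reply is that this is the instrument's cited scoring, described as validated in German, and that the caregiver survey is a separate instrument with its own answer labels and sources. Different scoring of two instruments is not in itself a contradiction, and whether the sources justify it cannot be checked here. That stands, and it is why the published score need not be displaced. It does not settle whether the 1/2 step is neutral between arms when the intervention itself may change which topics apply.

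The mechanism is also inferred. The article lists none of the items in the primary dimension, so it does not show that they touch the topics MCA raises, or how often newly diagnosed stage IV patients would call them not applicable. This stands too: f is unknown, and the table is a range, not an estimate.

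A reader might infer that the shift occurs in the MCA arm alone. The documents do not support that. Control patients also have a first conversation (Data collection), the clinic's routine consultations already disclose diagnosis and prognosis (Setting), and the same physicians treat both arms (Limitations and strengths). Only a net difference between arms matters.

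A reader might also infer that the primary result must be biased downward overall, or even reversed. That does not follow: needs moving from 3–5 to 2 lower the score as intended.

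Finally, supportive analyses are often left to a statistical analysis plan, and none is at hand. But the point concerns a scoring rule that the article itself states, and an unseen plan does not change that rule.

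**Conclusion.** The point holds in conditional form. As stated, the primary score places a satisfied need above a not-applicable one, although neither is unmet and the protocol merges the corresponding caregiver codes. If MCA produces more moves from 1 to 2 than standard care does, the primary comparison is pushed against MCA by 25f points: 2.5 points, half the target, at a net 10%, and the whole target at a net 20%.

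This rests on three assumptions: linear 0–100 rescaling of the patient score, a value of f that the documents do not supply, and, for the power figures, an unchanged SD. It does not show that such a shift will occur or which way the overall effect will go. Nor does it show an error in the sample size. It is worth acting on because the target is small relative to one coding step and the remedy is cheap.

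**What to change.** Keep the published 1–5 scoring as the primary outcome. Before any outcome data are seen:

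- pre-specify the same t1 model (treatment group and baseline value, same handling of missing values) on a patient score with codes 1 and 2 merged, at baseline as well as at t1, as a supportive analysis;
- state the numerical value that the merged category takes;
- report the distribution of codes 1 and 2 in the health system and information dimension, by arm, at t0 and t1.

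If the two models agree, the 1/2 step is not driving the result. If they differ, the table of codes shows why.

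The cost is one extra model and one table on data already collected. The downside is that merged scores are less comparable with published subscale means. The 5-point difference and SD of 7.4 should not be assumed to carry over to them, so that analysis should be read by its estimate and confidence interval.
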